## Abstract

**Background:**

Research on the motivational model proposed by Self-Determination Theory (SDT) provides theoretically sound insights into reasons why people adopt and maintain exercise and other health behaviors, and allows for a meaningful analysis of the motivational processes involved in behavioral self-regulation. Although obesity is notoriously difficult to reverse and its recidivism is high, adopting and maintaining a physically active lifestyle is arguably the most effective strategy to counteract it in the long-term. The purposes of this study are twofold: i) to describe a 3-year randomized controlled trial (RCT) aimed at testing a novel obesity treatment program based on SDT, and ii) to present the rationale behind SDT's utility in facilitating and explaining health behavior change, especially physical activity/exercise, during obesity treatment.

**Methods:**

Study design, recruitment, inclusion criteria, measurements, and a detailed description of the intervention (general format, goals for the participants, intervention curriculum, and main SDT strategies) are presented. The intervention consists of a 1-year group behavioral program for overweight and moderately obese women, aged 25 to 50 (and pre-menopausal), recruited from the community at large through media advertisement. Participants in the intervention group meet weekly or bi-weekly with a multidisciplinary intervention team (30 2 h sessions in total), and go through a program covering most topics considered critical for successful weight control. These topics and especially their delivery were adapted to comply with SDT and Motivational Interviewing guidelines. Comparison group receive a general health education curriculum. After the program, all subjects are follow-up for a period of 2 years.

**Discussion:**

Results from this RCT will contribute to a better understanding of how motivational characteristics, particularly those related to physical activity/exercise behavioral self-regulation, influence treatment success, while exploring the utility of Self-Determination Theory for promoting health behavior change in the context of obesity.

**Trial Registration:**

**Clinical Trials Gov. Identifier **NCT00513084

## Background

Prevalence of overweight and obesity in modern societies has increased rapidly. Recent reports indicate that 51.6% Portuguese adults are overweight or obese [1]. Obesity is a major public health problem, associated with a number of chronic disease risk factors [2]. Furthermore, overweight and obesity are stigmatizing conditions, especially for women, and are often associated with dysphoric states and psychological problems [3]. Weight loss is recommended as an important part of clinical management and extensive research supports the utility of including physical activity/exercise in weight reduction programs[4]. Unfortunately, the evidence shows that relatively little of the weight loss accomplished in treatment programs is maintained over the long-term [5]. Therefore, there is a strong need for research that identifies predictors of successful weight-loss *maintenance *and tests interventions to specifically promote weight stability after weight loss [6]. Additionally, considering the available evidence regarding behavioral correlates of successful weight loss, comparatively little is know regarding psychological processes associated with long-lasting weight management [7], namely sustained motivation.

The present research project aims at describing a randomized controlled clinical trial (RCT) conceived to test a novel obesity treatment program based on Self-Determination Theory (SDT). Herein, we seek i) to present the theoretical rationale of adopting SDT (and facets of Motivational Interviewing) to facilitate and explain sustained change in physical activity and body weight, and ii) to describe the actual intervention, at a level of detail that effectively allows its evaluation and replication. This is a recommendation from the Behavior Change Consortium [8] and other researchers [9], considering that intervention descriptions are often not specific about the techniques employed and that there is no clear correspondence between theoretical "inspiration" and adoption of particular behavior change techniques. Experimental research and increased theoretical and methodological clarity could accelerate the identification of effective behavior change techniques and the development of evidence-based-practice in health psychology and education. Unfortunately, few examples are currently available in the published peer-reviewed literature.

Primarily, we will evaluate the extent to which a more internal self-regulatory style, higher intrinsic motivation, and more internal perceived locus of causality (regarding exercise behavior) act as mediators of sustained exercise adherence and weight loss. Motives to exercise are also expected to mediate the impact of the intervention on behavioral outcomes; psychological, interpersonal, and health-related motives are hypothesized to positively predict long-term exercise participation. Secondly, individual differences in general causality orientations and perceived treatment climate will be evaluated as moderators of intervention effects; more successful participants are expected to show a more autonomous (less controlling) general orientation style and to describe the treatment interpersonal environment as more autonomy-supportive. A comparison group is included in the research design, to adequately test intervention-specific moderation and mediation hypotheses [10].

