According to SDT, a person will develop and maintain more self-determined motivation when the personal context around them is *autonomy supportive*. The idea of autonomy support refers to eliciting and acknowledging peoples' perspectives, supporting their initiatives, offering choice/options, and providing relevant information, while minimizing pressure and control. Previous research has demonstrated that when physicians are perceived by their patients as being autonomy supportive, patients report greater self-motivation for treatment adherence [17]. Another recent study, designed to test a SDT intervention for motivating tobacco cessation in a clinical trial [18], showed that intervention participants perceived greater autonomy support and reported greater autonomous and competence motivations than did controls, supporting the causal role of autonomy support in the internalization of more internal forms of regulation.

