### The Self-Determination Theory model for maintained behavior change

Figure 2 presents the self-determination model of health behavior change and the expected relationships among its key constructs. Central to the model is autonomous self-regulation for behavior change. Autonomy support, both experimentally manipulated and as perceived by patients, and also a participant's general autonomy orientation are predicted to enhance autonomous self-regulation and perceived competence. Autonomous self-regulation and perceived competence are in turn expected to increase maintained change of the health-risk behaviors [29].

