#### Promoting self-determination

The intervention was designed to establish an autonomy-supportive climate for the participants, regardless of their stage of change or their expectancies and efficacy. The overall goal was to bring each participant closer to making autonomous decisions about whether she wanted to change and how, and then help her cope with the consequences of her choices, whether she succeeded or failed. The following strategies were used as facilitators in enhancing autonomous motivation [15]:

**a) Offering a clear rationale **to adopt a specific behavior; presenting clear contingencies between behavior and outcome; building sustainable knowledge that supported informed choices, by using neutral language during interpersonal communication (e.g., "may" and "could", and not "should" or "must"); and acknowledging participants' feelings and perspectives.

**b) Acknowledging internal conflict **(usual patterns and habits vs. desire to adopt a new behavior); promoting opportunities for participants to indicate their reasons to change activity and nutrition patterns; exploring **perceived benefits and personal barriers**. Such decisional balance constructs have been shown to be important mediators of motivational readiness [33,34].

**c) Providing participants with a menu of options **and a variety of avenues for behavior change, supporting the presentation of tasks and choices with a clear rationale. Because different people have different behavioral preferences and barriers, this is expected to lead to greater long-term adherence, allowing each participant higher congruence between their values and goals, and their lifestyles.

**d) Promoting competence **by practicing skills necessary for completion of specific tasks, such as exercising at a given intensity or reading food labels. More than merely increasing knowledge, the aim was to promote the adoption of self-management skills such as self-monitoring, goal setting, building contingency plans, and managing time (reallocate time to spend it in ways that are more consistent with personal priorities). The intervention team consistently focused on participants' strengths, affirmed small steps as they were taken, and reinforced positive change, knowing that the feeling of competence grows from feedback inherent to the task (cues for objective success), social feedback (comments from others or comparisons to standards), and progression toward a distal goal.

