### Self-Determination Theory related instruments

General causality orientations were assessed with the *General Causality Orientations Scale (GCOS) *[58]. Exercise intrinsic motivation was measured with the *Intrinsic Motivation Inventory (IMI) *[27], adapted to specifically measure the dimensions of exercise interest/enjoyment, perceived competence, effort/importance and pressure/tension.

The *Locus of Causality for Exercise Scale (LCE) *[59] assessed locus of causality for exercise. The *Health Care Climate Questionnaire (HCCQ*) [20] measured participants' perceptions of the degree of autonomy support (vs. controllingness) of the relevant health-care providers. The *Exercise Self-Regulation Questionnaire (SRQ-E) *[60] assessed domain-specific individual differences in types of motivation or regulation (external, introjected, identified, and integrated). Finally, the *Exercise Motives Inventory (EMI-2) *[61,62] assessed exercise participation motives on five dimensions (psychological, interpersonal, health-related, body-related and fitness-related motives), including 14 subscales.

At baseline and treatment's end (12 months) individual interviews of approximately 45 minutes were also conducted. The addition of qualitative information to quantitative data (i.e., psychometric instruments) is an important and innovative aspect of this study's assessment plan. Due to space limitations, interviews are not described in detail herein.

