### Statistical analyses

Analysis will be conducted for completers-only and using an intent-to-treat model. Baseline data imputation for missing scores at follow-up will be employed by default. Despite limitations of any imputation strategy, this method is conservative and has been recommended before [63]. The use of these models is very important in clinical trials where completion is less than perfect, since completers-only analyses can be severely biased and underpowered [44].

For analysis of moderators and mediators, we will follow recommendations by Kraemer et al. [10]. Generally, for each primary outcome, linear models with be conducted to test for 1) main effect of intervention (I), 2) main effects of each moderator or mediator (M), 3) interactive effects of M and I, 4) overall effect of intervention (plus high vs. low M) and 5) effect of intervention for sub-groups of subjects at specific levels of M. A moderator will be defined as a baseline variable (thus uncorrelated with intervention) that interacts with intervention assignment to produce significant effects. The overall effect of intervention ("additive" effect of intervention and M) will represent the actual (clinical) impact of intervention participation in the presence of M. Finally, profiles of subjects with particular values of M may be identified who are responsive to this particular SDT-based intervention.

Measures of central tendency and distribution will be examined for body weight and psychosocial variables at the different measurement periods. Repeated measures ANOVA and ANCOVA General Linear Model will be used to assess change in dependent variables and to test for within-and between-group differences. Multiple regression analyses and recursive partitioning (signal detection methodology) [64] will be employed to identify characteristics/profiles associated with success, following the principles enunciated above.

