## Discussion

Despite the cumulative evidence for the positive role of regular physical activity and exercise in long-term weight management, it remains unclear why only about 20% of individuals seeking weight loss are able to successfully integrate activity behaviors into their lifestyles and achieve long-lasting weight control [6]. Since few data are available concerning exercise motivation in the context of weight control, studies in this domain are critical and we believe further application of SDT in the behavioral treatment of obesity is a potentially fruitful area to explore. On the other hand, although empirical data generally support the efficacy of research using motivational techniques, the underlying mechanisms for change remain largely unexplored. According to Bauman [67], if an intervention is not well implemented, it may not affect the proposed mediators and, as a consequence, outcomes may not be sufficiently improved. According to previous research [18,20,30], SDT should be useful in explaining the dynamics of motivation during the course of obesity treatment, providing direct empirical support for autonomy, competence, and perceived autonomy support as three of the psychological processes through which intensive behavioral treatment might operate.

Key innovative features of this study are: a theory-based intervention based on the principles of Self-Determination Theory, a unique setting and population (the first long-term RCT for weight loss conducted in Portugal), *a priori *selection of putative moderators and mediators responsible for therapeutic change, high emphasis on physical activity/exercise, both as exposure and outcome, a systematic evaluation of a large range of potential determinants of outcomes, objective measurements of physical activity (via accelerometry), and precise measure of body composition changes (via DXA).

Results from this study are expected to contribute to a better understanding of how motivational characteristics, particularly those related to physical activity/exercise, influence treatment success during obesity treatment, while exploring the utility of Self-Determination Theory for promoting health behavior change in this most important context. That theory should evolve based on rigorous empirical evidence and that applied intervention research is one of the best ways to evaluate and refine theory [31].

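### Perceived treatment climate is named as a moderator, but it arises after treatment begins and so fails the plan's own definition of a moderator

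*Protocol article*

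**What the plan says.** The hypotheses at the end of the Background put two variables in one class: "individual differences in general causality orientations and perceived treatment climate will be evaluated as moderators of intervention effects". The same sentence adds that more successful participants are expected "to describe the treatment interpersonal environment as more autonomy-supportive".

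The Statistical analyses section gives the rule for that class: "A moderator will be defined as a baseline variable (thus uncorrelated with intervention) that interacts with intervention assignment to produce significant effects". It lists five steps, worded for each moderator or mediator (M). They include the intervention effect combined with high versus low M (step 4) and the intervention effect in sub-groups at particular levels of M (step 5). It then looks ahead to profiles of women who respond to this intervention.

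Climate is measured with the Health Care Climate Questionnaire (HCCQ), which "measured participants' perceptions of the degree of autonomy support (vs. controllingness) of the relevant health-care providers" (Self-Determination Theory related instruments). Measurements lists visits at baseline and at 4, 12, 16, 24 and 36 months, but the article does not say at which of them the HCCQ is given.

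**The concern.** The two statements cannot both be followed. A woman can describe the treatment environment only after meeting it, so the variable named in the Background is not a baseline variable. Nor can it be expected to be uncorrelated with assignment, because changing the climate is what the intervention is for.

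This matters for interpretation. Among women who report a supportive climate, those in the intervention arm and those in the comparison arm reached that report by different routes, and they need not be alike in other respects that affect outcome. A contrast between them is no longer protected by randomisation. It may present how the treatment works as a finding about who benefits. The Discussion lists the a priori choice of moderators and mediators among the study's key innovative features, so the classification carries weight.

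**Working it through.** **Text against text.** The plan states no figure for this point, so the first check is whether climate can satisfy the definition.

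- Required: measured at baseline and uncorrelated with assignment (Statistical analyses).
- Timing: the variable is a description of the treatment environment (Background). A baseline HCCQ score, if taken, would not measure that.
- Relation to assignment: "The intervention was designed to establish an autonomy-supportive climate for the participants" (Promoting self-determination). The theoretical model names "Autonomy support, both experimentally manipulated and as perceived by patients" as an influence on self-regulation and competence (section on the SDT model for maintained behavior change). An earlier trial of an SDT intervention is cited because "intervention participants perceived greater autonomy support and reported greater autonomous and competence motivations than did controls" (Theoretical rationale).
- Role: the Discussion lists "autonomy, competence, and perceived autonomy support as three of the psychological processes through which intensive behavioral treatment might operate". That is a mediator's role.

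Climate fails both parts of the definition. General causality orientations, the other moderator named, describe a general personal disposition that can be measured at baseline, and they are not affected.

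**Illustration of size.** The true effect is set at 0.56 SD, the 1-year physical activity effect in Sample size and power: (300 − 50)/450 = 0.556 with the mean of the two SDs, or 250/452.8 = 0.552 with the pooled SD. Everything else is assumed.

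Model: M = a·I + c·U + error, with within-arm variance of M equal to 1; Y = τ·I + b·M + g·U + error. I is arm, M climate, U an unmeasured shared cause and a the shift in climate by arm. There is no true interaction. The coefficient of I adjusted for M is τ − a·c·g when c is the same in both arms. Median-split results come from simulation with 2,000,000 subjects per scenario.

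(a) Climate has no effect on outcome: τ = 0.56, b = 0, c = g = 0.5, so the adjusted effect is 0.56 − 0.25a.

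| Shift a (SD) | Adjusted effect | Effect within each median-split half |
|---|---|---|
| 0.3 | 0.485 | about 0.51 |
| 0.5 | 0.435 | about 0.48 |
| 0.8 | 0.36 | about 0.44 |
| 1.0 | 0.31 | about 0.40 |

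The correlation of arm with climate, (a/2)/√(1 + a²/4), runs from 0.15 to 0.45 over these shifts; the definition requires 0.

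The scaling also matters. If the error in M, rather than M itself, has unit variance, the 0.8 SD row becomes 0.56 − 0.8 × 0.25/1.25 = 0.40.

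(b) Climate is a full mediator: τ = 0, b = 0.56/a, with a from 0.5 to 1.0. Without confounding the adjusted effect is 0, and the halves show about 0.20 to 0.21. With c = g = 0.5 the adjusted effect is −0.25a, that is −0.125 to −0.25, and the halves show 0.05 to 0.13.

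(c) The shared cause relates to climate differently by arm: c = 0.5 in the intervention arm, 0.1 in the comparison arm, b = 0, g = 0.5. The slopes of Y on M are 0.25 and 0.05, so an interaction of 0.20 per SD of climate appears where none exists. At a = 0.5 the effect looks like 0.67 in the high half and 0.35 in the low half.

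(d) Control, as for a true baseline variable: a = 0 and the same c in both arms. Both halves return about 0.56 and the interaction is 0.

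**The case against.** The strongest reply is that the analysis section already holds the right rule. If its definition governs, climate is simply not tested as a moderator, and the Background contains a mislabel. The Background also introduces this hypothesis second, after mediation, and its wording about more successful participants reads more like a predictor of success than an effect modifier. These points lower the severity. They do not remove the contradiction: the Background still commits to climate as a moderator, and the steps are written for moderators and mediators alike, so an analyst could report intervention effects at levels of climate and still be following the text.

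It is also fair that the article gives no HCCQ timing. That the rating follows the start of treatment is an inference, though a secure one given what is rated.

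Some stronger readings are not supported:

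- A reader might infer a definite bias, such as the 36% loss in the 0.8 SD row (0.20/0.56). That is one assumed scenario, and neither the shift nor the loadings are in the article.
- A reader might infer that false sub-group differences must follow. In scenarios (a) and (b) the two halves agree; what appears is attenuation. A spurious interaction appeared only in (c), which needs a further assumption.
- A reader might infer that steps 4 and 5 must be dropped for every mediator, or that a particular mediation method is required. The article says the steps apply in general and follow cited recommendations, and such detail is commonly left to a fuller plan.

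**Conclusion.** The point holds and should be fixed: the classification of perceived treatment climate is wrong as written. The contradiction rests on the text alone and needs no assumed number. Testing climate as a moderator, or reporting intervention effects at its levels, conditions on a variable affected by assignment. Such contrasts are not randomised and cannot show who responds.

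The size is uncertain. Under the assumptions in (a), a true 0.56 SD becomes about 0.49 to 0.31 SD after adjustment for climate. Under unconfounded full mediation it becomes about 0, which is a correct direct effect but would mislead if read as the effect of the intervention in women with a given climate.

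A reader might infer that the trial's main result is at risk. It is not: the overall comparison of the randomised groups does not condition on climate.

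**What to change.** - In the Background hypotheses, move perceived treatment climate from moderator to mediator or process variable, in line with the theoretical model and the Discussion. Alternatively, call it a predictor of success within the intervention arm.
- In Statistical analyses, limit moderator tests, and sub-group effects offered as evidence of who responds, to variables measured before randomisation, such as general causality orientations.
- Label any analysis at levels of perceived climate as non-randomised and exploratory.

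The cost is wording only. The HCCQ is already in the assessment battery, and neither the randomised comparison nor the sample size changes.
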